### **13.3 Remainder samples and archive samples**

Remainder of serum (and plasma) of the screening is meant for repeated analysis in case of unexplained abnormal values and will be stored until subject selection has been completed.

Remainder samples of the study period will be discarded after approval of the final report of the study by the sponsor. Archive samples and non-used samples meant for repeat analysis, pm analysis or additional analysis (see section 11.2.1) of the study period will be discarded 5 years after approval of the final report of the study by the sponsor.

## 14 Documentation

The documentation of this study consists of the study protocol, correspondence, report, raw data, source documents or authenticated copies of these.

For privacy reasons, documents containing data of individual subjects will be identified only by their pre-entry or entry number.

## 15 Data management and statistics

### 15.1 Data management

The following SAS datasets will be prepared:

1. Pre-screening parameters
2. Body weight (days 01, 15, 29, 43)
3. Fasting homocysteine (days 01, 13, 15, 29, 41, 43)
4. Homocysteine after methionine (days 01, 15, 29, 43)
5. Blood lipids and liver enzymes (days 13, 15, 41 and 43)
6. Vitamin B6, B12 and folic acid (days 13, 15, 41 and 43)
7. Betaine, dimethylglycine, choline (days 01, 15, 29 and 43)

For data set 1 raw data will partly be delivered on paper and entered using double data-entry and partly in electronic format. For data set 2 raw data will be delivered on paper and entered using double data-entry. For data set 3, 4, 5, 6 and 7 raw data will be delivered in electronic format /on-line.

Raw data will be registered and will be converted to SAS data. All transformations and changes in datasets will be controlled and registered. Locked datasets will be electronically transferred to the sponsor.

### 15.2 Missing values

After completion of the clinical part of the study and before start of datamanagement the principal investigator will decide what has to be done with missing values and will inform datamanagement. Decisions will be described in the report.

### 15.3 Statistical analysis

#### 15.3.1 *Descriptive parameters*

Subject characteristics, adverse events and compliance will be presented descriptively.

#### 15.3.2 *Derived parameters*

For all fasting parameters (homocysteine, blood lipids, liver enzymes, B-vitamins) determined on day 13 and 15 as well as on days 41 and 43 mean values will be used for statistical analysis.

The increase of plasma homocysteine after methionine loading will be calculated at day 01, 15, 29 and 43 by subtracting the value at 6h from the value at 0h (pre-loading).

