#### **Statistical analysis**

- Descriptive : Subject characteristics, adverse events, compliance
- ANOVA: Analysis will be carried out with subjects and treatment as factors on body weight, fasting plasma homocysteine, increase in plasma homocysteine (6h) after methionine loading after single dose, increase in plasma homocysteine (6h) after methionine loading after 14d consumption, blood lipids, liver enzymes and creatinine, vitamin B6, B12, folate, betaine, dimethylglycine and choline

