## 6 Objective of the study

The objectives of the present study are

- To investigate the effect of daily intake of about 2.5 g choline on fasting plasma homocysteine
- To investigate the effect of daily intake of about 2.5 g choline on post-methionine loading plasma homocysteine
- To investigate the effect of single intake of about 1.25 g choline on post-methionine loading plasma homocysteine

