#### Plasma homocysteine following methionine loading

The standard deviation of the response (concentration of homocysteine at  $t=6$  h after methionine loading minus the concentration at  $t=0$  h) over the intervention period in the betaine group (1.5 g/d of betaine) was 6.3  $\mu\text{mol/L}$ . The decrease in homocysteine concentration at  $t=6$  h after methionine loading in the betaine group relative to placebo was 6.3  $\mu\text{mol/L}$ . With 26 subjects we are able to detect a statistically significant decrease in post-methionine loading homocysteine concentration of 4.2  $\mu\text{mol/L}$  with a power of 90% ( $\alpha=0.05$ , 2-sided test). This is similar to the decrease that was observed after a single dose of 0.75 g betaine in study 3818. With a power of 80% ( $\alpha=0.05$ , 2-sided test) a decrease of 3.6  $\mu\text{mol/L}$  can be detected.

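### Section 15.3.2 derives the post-methionine increase as 0 h minus 6 h, the reverse of section 9.2, so the variables for two of the three objectives carry the wrong sign

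*Protocol*

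**What the plan says.** Section 15.3.2 (Derived parameters) names the variable and its days: "The increase of plasma homocysteine after methionine loading will be calculated at day 01, 15, 29 and 43". It then gives the rule: "by subtracting the value at 6h from the value at 0h (pre-loading").

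Section 9.2, under the post-loading sample-size paragraph, defines the response as the concentration at 6 "h after methionine loading minus the concentration at" 0 h, and expresses the expected effect as a decrease.

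The synopsis (Statistical analysis) lists among the ANOVA variables the "increase in plasma homocysteine (6h) after methionine loading after single dose, increase in plasma homocysteine (6h) after methionine loading after 14d consumption". These correspond to two of the three objectives in section 6: "To investigate the effect of daily intake of about 2.5 g choline on post-methionine loading plasma homocysteine" and "To investigate the effect of single intake of about 1.25 g choline on post-methionine loading plasma homocysteine". The remaining objective concerns fasting homocysteine, which needs no subtraction.

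Section 15.3.3 tests at the 0.05 level, with a two-sided t-test of treatment means after the ANOVA.

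**The concern.** Subtracting A from B gives B minus A. The rule in 15.3.2 therefore yields 0 h minus 6 h, which disagrees both with the variable's own name and with section 9.2. No other section of the protocol corrects it.

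The direction of a result matters here because the test is two-sided: a small p-value says that the treatments differ, and only the sign of the estimate says which way. Fasting homocysteine keeps its natural sign, so a genuine lowering on both measures could be tabulated with opposite signs and look inconsistent.

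Section 20.1 requires the study to follow the protocol. A programmer who codes 15.3.2 as written complies and stores the wrong sign; one who codes the evident intention departs from the text. The derived data also change hands. One department of the research organisation analyses and another drafts the report (synopsis, Responsibilities), locked datasets go to the sponsor (15.1), and the sponsor writes the publication (section 17). A variable whose name and written definition have opposite signs is easy to misread at such hand-overs.

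**Working it through.** **Inputs.** From section 9.2: 26 subjects; SD of the response "over the intervention period in the betaine group (1.5 g/d of betaine) was 6.3" µmol/L; detectable decrease 4.2 µmol/L at 90% power and 3.6 µmol/L at 80% power; two-sided α = 0.05. From the ANOVA table in 15.3.3: 24 residual degrees of freedom.

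**1. The plan's own figures.** Take 6.3 as the SD of the paired difference, which is the reading that reproduces the stated power.
- SE = 6.3/√26 = 6.3/5.099 = 1.236 µmol/L.
- Difference 4.2: noncentrality 4.2/1.236 = 3.40; power 90.4% with 25 df, 90.3% with 24 df (stated: 90%).
- Difference 3.6: noncentrality 3.6/1.236 = 2.91; power 80.0% with 25 df, 79.8% with 24 df (stated: 80%).

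The figures reproduce, so 4.2 µmol/L is a sound planning value for showing the effect of the sign.

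**2. The two definitions.** Write C0 and C6 for the concentrations at 0 h and 6 h.
- Section 9.2: I = C6 − C0.
- Section 15.3.2, literally: D = C0 − C6 = −I.

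**3. The treatment effect.** If choline minus reference in I is Δ, then in D it is −Δ.
- Δ = −4.2 becomes +4.2 µmol/L.
- Δ = −3.6 becomes +3.6 µmol/L.

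**4. What does not change.** Multiplying every observation by −1 leaves every sum of squares in the ANOVA as it was, so F is unchanged. The t statistic changes sign only, so the two-sided p-value is unchanged. A confidence interval (L, U) becomes (−U, −L), with the same width. For an estimate of −4.2 and SE 1.236 with 24 df, the half-width is 2.064 × 1.236 = 2.55, so −6.75 to −1.65 becomes +1.65 to +6.75. Power and sample size do not depend on the sign.

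**5. Illustration on simulated data.** Assumed values, not from the protocol: 26 subjects, mean rise about 25 µmol/L on reference, true choline effect −4.2 µmol/L, and error SD 4.45 per loading, so that the paired difference has SD 4.45 × √2 = 6.29.

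| Rule | Reference mean | Choline mean | Choline − reference | t | F | p |
|---|---|---|---|---|---|---|
| 6 h − 0 h (9.2) | +24.6 | +20.0 | −4.67 | −4.49 | 20.15 | 0.00014 |
| 0 h − 6 h (15.3.2) | −24.6 | −20.0 | +4.67 | +4.49 | 20.15 | 0.00014 |

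The test results are identical. The signs of the means and of the difference are reversed.

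**The case against.** The strongest reply is that the intention is plain and the harm limited. The word increase in 15.3.2, the same word in the synopsis and the explicit definition in 9.2 all point to 6 h minus 0 h. This stands, and makes a drafting slip the likely explanation. It does not make the written rule right, and 15.3.2 is the place an analyst would look for it.

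A reader might infer that the error would pass unnoticed because p-values do not move. The documents do not support that. A rise after loading is expected (section 12.6 says it will not count as an adverse event), so a table of increases with negative means under both treatments would be conspicuous.

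A reader might also infer that the trial would necessarily report choline as raising post-load homocysteine. That does not follow. Section 15.3.3 compares treatment means and prescribes no signed choline-minus-reference contrast. Anyone looking at means such as −24.6 and −20.0 could see the smaller excursion on choline. The misreading is possible, not built in.

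Nor would it be right to put the possible distortion as high as 6.3 µmol/L. In section 9.2 that figure is the earlier betaine result, described as a fall in the 6 h concentration. It is not a planning difference for choline, nor explicitly a difference in the increment.

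Finally, the error is recoverable. Section 15.1 keeps the fasting and post-load values in separate datasets, and section 16 puts individual data in the report's appendices. An analysis plan not shown here might fix the sign, but the protocol does not leave the rule open: it states it, and states it the wrong way round.

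**Conclusion.** The point holds as a sign error in a stated analysis rule, and it should be fixed. It affects the derived variable at all four loadings and hence the post-load results for the single-dose and 14-day objectives; the fasting objective is untouched. The estimate keeps its magnitude and reverses its sign. This rests on two conditions: that the rule is applied literally, and that the result is presented as a difference in increase. There is no consequence for significance, precision, power, sample size or data collection, so the point ranks below a defect that would change the trial's inference.

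**What to change.** Reword the second paragraph of section 15.3.2 so that the increase is calculated at days 01, 15, 29 and 43 as the 6 h value minus the 0 h (pre-loading) value, matching section 9.2. Check that the derivation code follows the corrected sentence.

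The cost is one sentence in the protocol and at most one line of SAS code. Design, visits, sampling and sample size are unaffected. The change is best made before the derived variables are programmed.

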#### 15.3.3 *Analysis*

ANOVA will be performed using the below given table. If the analysis of variance indicates a treatment effect ( $p < 0.05$ ), comparisons between treatment means of the parameters will be performed using a 2-sided Student t-test.

In case of unequal group sizes, General Linear Models (GLM) procedure will be used in stead of ANOVA.

*ANOVA table*

| Source of variation | Degrees of freedom |
|---------------------|--------------------|
| Subjects            | 25                 |
| Periods             | 1                  |
| Treatments          | 1                  |
| Residual error      | 24                 |
| Total               | 51                 |

Based on results and discussion with co-researchers, sponsor and remarks of referees additional statistical analysis may be performed. Additional statistical analysis will be described in an amendment to the protocol.

In all statistical tests performed, the null hypothesis (no treatment effect) will be rejected at the 0.05 level of probability.

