#### 8.2.2 *Blinding and unblinding*

All treatments will be blinded for the:

1. Subjects
2. Sponsor
3. Principal investigator, medical investigator and their staff involved in the conduct of the study
4. Members of the Medical Ethics Committee of TNO (TNO-METC)
5. Inspectors involved in the inspection of the clinical part of the study

Only the person who attributed the codes “A” or “B” to the test and reference substance will know the meaning of the codes and will supply the principal investigator at TNO with a sealed envelope containing the key of the codes.

Before the start of the clinical part of the study, the statistician will inform the dietician and the senior research nurse in writing about the allocation to entry number.

Before the clinical part of the study, the statistician will inform the dietitian responsible for labelling of the study substances, in writing of the treatment allocation of the subjects (pre-entry number, entry number and treatment).

The statistician will supply the principal investigator with sealed envelopes per subject, containing the treatment allocation. The principal investigator informs the medical investigator about the place of storage of, and access to these envelopes. During the study, only medical urgency will allow the medical investigator to open an envelope for breaking the code only for the subjects needed. When an envelope is opened, date, time and reason will be documented.

The statistician will unblind the study after the database is closed and after the

1. AEs have been interpreted and reported by the medical investigator to the principal investigator,
2. Laboratory reports on the analyses of the study parameters have been authorized,
3. Decisions on subject or data exclusions have been made.

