## 16 Reporting

The CRO will draft a report (in English), including a Summary, Introduction, Methods section and Description of results section. The report will include deviations from the protocol and safety data. Results of all parameters as specified in this protocol will be presented in summarizing tables. Individual data will be presented in appendices. The final report will contain an audit certificate by the Quality Assurance Unit (QAU) of the TNO Nutrition and Food Research and a statement on GCP compliance signed by the principal investigator.

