## 20 Ethics and quality

### 20.1 General

The study will be conducted in compliance with the protocol and all amendments to the protocol. The protocol and all amendments to the protocol effecting the design, rationale or objectives of the study, or the burden of or health risks for the volunteers will only be implemented after written approval of the TNO METC (or the CCMO when applicable) and the sponsor. All amendments will be sent to the Medical Ethics Committee for information or approval.

The study, except for the analysis of betaine, dimethylglycine and choline in plasma samples, will be conducted according to:

1. The current revision of the World Medical Association Declaration of Helsinki. 52nd WMA General Assembly, Edinburgh, Scotland, October 2000.
2. The ICH Guidelines for Good Clinical Practice (ICH Topic E6, adopted 01-05-1996 and implemented 17-01-1997)
3. Regulations on Medical Research involving Human Subjects (Medical Research involving Human Subjects Act, Wet medisch-wetenschappelijk onderzoek met mensen, WMO 1999)
4. The current national regulations.

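### Section 15.3.3 applies the 0.05 rejection rule to every test, including analyses added because of the results after unblinding

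*Protocol*

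**What the plan says.** Three consecutive statements in Protocol section 15.3.3 (Analysis) matter here.

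- What may trigger further analysis: "Based on results and discussion with co-researchers, sponsor and remarks of referees additional statistical analysis may be performed".
- How it is recorded: "Additional statistical analysis will be described in an amendment to the protocol".
- How it is judged: "In all statistical tests performed, the null hypothesis (no treatment effect) will be rejected at the 0.05 level of probability".

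Section 8.2.2 (Blinding and unblinding) fixes the timing: "The statistician will unblind the study after the database is closed and after the" adverse events have been interpreted and reported, the laboratory reports authorized, and the exclusions decided. Section 20.1 (General) gives the standing of amendments: "The study will be conducted in compliance with the protocol and all amendments to the protocol".

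The protocol does not require an amendment that adds an analysis to predate unblinding. It also does not describe analyses added later as post hoc or exploratory.

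**The concern.** The 0.05 rule is a fair decision rule for a test fixed before anyone sees the data by treatment. It is not one for a test picked because the data suggested it. Section 15.3.3 covers both kinds with one sentence and no exception.

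Suppose the planned comparison of fasting homocysteine shows no effect. The data already collected allow several other comparisons:

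- day 13 or day 15 (and day 41 or 43) taken singly, instead of the two-day mean that section 15.3.2 prescribes;
- change from the start of each period, using the day 01 and day 29 samples;
- splits by screening homocysteine or smoking, the factors that restrict the randomization in section 12.3.

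The protocol plans none of these. But if one were added after the planned result was known and gave p < 0.05, section 15.3.3 as written would direct that the null hypothesis be rejected, just as for the planned test. What is at stake is what the trial may claim, not whether such analyses may be run.

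**Working it through.** **Step 1: order of events.** Section 8.2.2 places unblinding after database closure and after decisions on exclusions. Referees comment on reported results, and results by treatment require the code. Analyses triggered by either therefore come after unblinding. Section 8.2.2 puts exclusion decisions before unblinding; no matching requirement exists for the choice of analyses.

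**Step 2: inputs.**

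- From the protocol: two-sided tests at 0.05 each, with no adjustment stated (15.3.3); 26 subjects in a cross-over (9.2).
- Assumed: the number k of added tests, and the correlation r between test statistics. The protocol gives neither, so ranges are shown.

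**Step 3: the plan's own figure.** One planned test, no added tests: false-positive rate 5%, as stated.

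**Step 4: independent added tests.** The chance of at least one false rejection is 1 − 0.95^(k+1).

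- k = 1: 1 − 0.95² = 9.75%
- k = 5: 1 − 0.95⁶ = 26.5%

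**Step 5: correlated added tests.** For k+1 equicorrelated standard normal statistics, the rate is the probability under the null that at least one exceeds 1.96 in absolute value.

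| Added tests k | r = 0 | r = 0.5 | r = 0.8 |
|---|---|---|---|
| 0 | 5.0% | 5.0% | 5.0% |
| 1 | 9.8% | 9.1% | 7.8% |
| 3 | 18.5% | 15.6% | 11.4% |
| 5 | 26.5% | 20.7% | 13.9% |
| 10 | 43.1% | 30.4% | 18.0% |

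**Step 6: an example from this trial.** Take the planned two-day mean of fasting homocysteine and add day 13 (with its counterpart, day 41) alone. Assume that the treatment difference within a subject has a period component with SD 1.2 and a day component with SD 1.0.

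- Variance of the single-day difference: 1.44 + 1.00 = 2.44
- Variance of the two-day mean difference: 1.44 + 0.50 = 1.94
- Covariance of the two: 1.44 + 0.50 = 1.94
- Correlation: √(1.94 / 2.44) = 0.89

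At r = 0.89 the rate for the planned test plus this one is 7.1%. A null simulation with 26 subjects and the same assumed SDs gives about 5% for the planned test, about 7% after adding day 13, and about 9% after also adding day 15.

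**Step 7: what these figures do and do not measure.** They count a fixed number of tests, all run. Under section 15.3.3 neither the number nor the kind of added test is fixed, so the protocol puts no upper limit on the rate.

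**The case against.** The best defence is that the text is open about what it does. It calls these analyses additional, says that they arise from the results, and requires an amendment; section 20.1 sends all amendments to the ethics committee for information or approval. Further analysis at a referee's request is ordinary practice. This stands, and three stronger readings that a reader might infer fail.

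- **That the amendment route conceals the origin of these analyses.** The documents do not support this. An amendment sent to the ethics committee is a record, and the fix should keep it.
- **That the protocol gives added analyses confirmatory status, or will report them as pre-specified.** It never uses the word confirmatory. Section 16 says "Results of all parameters as specified in this protocol will be presented in summarizing tables", which concerns parameters and does not mention amendments. Section 20.1 is about compliance in conduct. What the text does establish is narrower: a shared rejection rule with no distinction by timing.
- **That any single added test raises the error rate beyond 1.5 times alpha, that is 7.5%.** The day 13 example gives 7.1%.

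It can also be said that an exploratory label is usually left to the statistical analysis plan. That would answer a mere omission. Here the protocol states a rule for all tests, and a label set elsewhere would sit beside text that still directs rejection at 0.05.

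Finally, the inflation figures resemble those for the three objectives in section 6, which are not ranked. That is a separate matter: naming one primary endpoint would leave the rule on added analyses unchanged.

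**Conclusion.** The point holds in a limited form. Section 15.3.3 extends the 0.05 rejection rule to analyses that may be chosen after unblinding on the basis of the results, and does not set them apart from analyses fixed earlier. For such tests 5% is not the false-positive rate.

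The size is illustrative. For one planned test, the rate goes from 5% to about 9% with one added test and about 21% with five at an assumed correlation of 0.5. With five added tests it ranges from about 14% at correlation 0.8 to 26.5% under independence. One closely correlated addition gives about 7%. These figures rest on an assumed number of tests and assumed correlations and, for the day 13 example, on assumed SDs.

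No figure in the protocol is wrong on this account. Post hoc analysis is legitimate; the fault is giving it the decision rule of the planned tests.

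**What to change.** Amend section 15.3.3 in two places.

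1. Limit the rejection sentence: the 0.05 rule applies to analyses specified in the protocol, or in amendments dated before unblinding.
2. Add a rule for the rest: analyses added after unblinding, whether prompted by results, discussion with the sponsor or co-researchers, or referees' remarks, are documented in a dated amendment or in the report, labelled post hoc and exploratory, and presented as estimates with 95% confidence intervals.

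This keeps the amendment trail and prevents no analysis. The cost is two or three sentences, with no new data or subjects. The small downside is that analyses requested later by the sponsor or referees cannot support claims of statistical significance.
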